#### Subgroup analyses

Planned subgroup analyses include:Gestational age at birth (born before 28 weeks, between 28 and 32 weeks, and after 32 weeks)Gender of the newborn

For those subgroups, we will repeat:The primary analysis, using the confidence interval for the difference between full-dose and half-dose.The following secondary analysis: death, IVH grade 3 and 4, NEC grade ≥ 2, or retinopathy of prematurity treated by anti-VEGF or laser, survival without severe RDS, IVH grade 3 and 4, NEC grade ≥ 2, or retinopathy of prematurity treated by anti-VEGF or laser, using 2-sided tests, as stated above.

For both those analyses, we will use the Holm-Bonferroni method to adjust for multiplicity of analyses [58].

Statistical analyses will be performed with SAS (V.9.4; SAS institute) and R (V 3.4.2) software.

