#### Allocation of treatment and blinding

After obtaining maternal consent, randomisation is performed just before the second injection, using a web-based application and a secured access, in a one-to-one ratio to the full or half dose groups according to a computer-generated list of randomly permuted blocks. The randomisation is stratified by maternity units and gestational age (before or after 28 weeks). The randomisation list is centrally computer-generated and a web-based application ensures proper allocation concealment. The allocation sequence is not available to any member of the research team until the database will be completed and locked. Patients, care providers and outcome assessors are masked to assignment. A study number is allocated to the woman corresponding to a treatment pack, each of which looks identical and contains two opaque study-labeled vials.

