### Statistical analysis

#### Sample size

To study the non-inferiority of the 50% reduced betamethasone dose regimen, we will test the alternative hypothesis that the difference in failure rate between the half-dose and the full-dose arm do not exceed 4% (corresponding to a Relative Risk of 1.20). This non-inferiority margin has been obtained through a consensus between the investigators of the GROG, neonatologists and the methodologists of the study, considering that a 4% difference is the smallest value that would be clinically relevant between arms and correspond to the preservation of a 70% of the effects of the full dose betamethasone regimen over placebo. Indeed, in the French Epipage2 study (2011) [51], 62% of the neonates exposed to antenatal betamethasone and born before 32 weeks of gestation from a singleton pregnancy received exogenous surfactant. Assuming that 33% (conservative hypothesis) of the randomised women will indeed deliver before 32 weeks, we estimated that 20% of the included pregnant women receiving the full betamethasone dose regimen would have a neonate with severe RDS, defined as the need for exogenous intra-tracheal surfactant. According to the literature, ACS is responsible for an average relative risk of RDS of 0.66 (95% CI 0.56 to 0.77), compared to placebo [8, 52]. Assuming a prevalence of severe RDS of 20% in the full dose betamethasone regimen, to preserve 67% of the upper bound for the historical difference between full dose and placebo (i.e. 0.67 x (0.20–0.20/0.77)) gave a margin of 4% (or expressed as Relative Risk (20 + 4) / 20 = 1.20). Thus, 1571 patients in each treatment group are required to test the non-inferiority hypothesis, with a 1-sided type-1 error of 0.025, a power of 0.80, and a non-inferiority margin equal to 4% [53].

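### Subgroups by gestational age at birth repeat the primary non-inferiority analysis with a margin set for a 20% failure rate, while the baseline gestational-age stratum goes unused

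*Protocol article*

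**What the plan says.** In the protocol article, Subgroup analyses lists two factors: "Gestational age at birth (born before 28 weeks, between 28 and 32 weeks, and after 32 weeks" (three bands) and newborn sex. Within each it repeats "The primary analysis, using the confidence interval for the difference between full-dose and half-dose", together with several secondary outcomes under two-sided tests, and adds: "For both those analyses, we will use the Holm-Bonferroni method to adjust for multiplicity of analyses".

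Allocation of treatment and blinding states that "randomisation is performed just before the second injection", and: "The randomisation is stratified by maternity units and gestational age (before or after 28 weeks". That stratification factor does not appear among the subgroups.

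The only margin in the article is in Sample size. The hypothesis is that "the difference in failure rate between the half-dose and the full-dose arm do not exceed 4% (corresponding to a Relative Risk of 1.20", tested "with a 1-sided type-1 error of 0.025, a power of 0.80, and a non-inferiority margin equal to 4" percentage points. It rests on an overall rate: "we estimated that 20% of the included pregnant women receiving the full betamethasone dose regimen would have a neonate with severe RDS". That rate is built from a 62% surfactant rate in singletons born before 32 weeks and a 33% share of women delivering before 32 weeks. The Interim analysis section uses the same three birth-age bands for the safety outcomes and notes that their expected prevalence differs between bands.

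**The concern.** Two features of the subgroup plan sit badly together.

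First, gestational age at birth is not known when women are allocated. Comparisons within birth-age bands are therefore not protected by randomisation as comparisons within a baseline stratum are. A baseline gestational-age factor exists, is recorded for every woman and is balanced by design, but the plan does not use it here.

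Second, the absolute margin equals a relative risk of 1.20 only at a 20% control rate. The birth-age bands are where the control rate moves furthest from 20%. If 4 points is the yardstick in each band, it is very strict in the early bands and may be very lenient in the late one.

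At stake is how the subgroup results would be read. The display could show non-inferiority in late births and not in early ones, where nearly all the events lie, even if the relative effect were the same throughout.

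**Working it through.** **Inputs from the article (Sample size):** 1571 per arm; one-sided alpha 0.025; power 0.80; margin 0.04; control rate 0.20 overall and 0.62 before 32 weeks; share born before 32 weeks 0.33.

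**Assumptions, not in the article:** the share of births under 32 weeks that are before 28 weeks (15-35%); the rate before 28 weeks (75-95%); the rate after 32 weeks (0.5-3%); a Holm family of five subgroup levels (three age bands, two sexes), so that the strictest step is 0.025/5 = 0.005. Later Holm steps are less strict, up to 0.025.

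**Plan's own figure.** n = 2 × 0.20 × 0.80 × (1.960 + 0.842)² / 0.04² = 1569.8, so 1570 per arm against the stated 1571. It reproduces; power at 1571 is 80.0%.

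**Implied rates by band.** 0.33 × 0.62 = 0.2046, which already accounts for the whole 20%. The implied rate after 32 weeks is (0.20 − 0.2046)/0.67 = −0.007, that is, about 0. Arm sizes: 1571 × 0.33 ≈ 518 before 32 weeks and 1571 × 0.67 ≈ 1053 after.

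**Formula.** Probability of passing = Φ((0.04 − d)/SE − z), where d is the true difference (half minus full dose), SE = √[(p₁q₁ + p₂q₂)/n], and z = 1.960 at 0.025 or 2.576 at 0.005.

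**Before 32 weeks pooled (62%, 518 per arm, equal arms).**
- 4 points is a relative risk of 0.66/0.62 = 1.06.
- SE = √(2 × 0.62 × 0.38/518) = 0.0302. The 95% half-width is 1.96 × 0.0302 = 5.9 points, wider than the margin.
- Pass probability: Φ(1.326 − 1.960) = 26%; at 0.005, Φ(1.326 − 2.576) = 11%.
- For 80% power: 2 × 0.62 × 0.38 × 7.849/0.0016 = 2312 per arm.
- For contrast, a relative risk of 1.20 at 62% is 12.4 points, and power against that would be 98%. The choice of scale alone decides the result.

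**The two planned early bands (equal arms, assumed splits).**
- Before 28 weeks: 8-42% at 0.025 and 2-20% at 0.005. With a 25% share and an 85% rate (about 130 per arm): 14.5% and 5%.
- 28 to 32 weeks, with its rate set so that the two bands average 62%: 18-23% at 0.025 and 6-9% at 0.005.
- Both bands passing: about 2-8% at 0.025 and about 1% or less at 0.005.
- If half of these births were before 28 weeks, the bands would pass 18-55% and 15-17% of the time at 0.025.

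**After 32 weeks (1053 per arm).** With equal arms the test passes at least 99.7% of the time at control rates up to 3%. If the half dose is truly worse:

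| Assumed control rate | Doubled, 0.025 | Doubled, 0.005 | Tripled, 0.025 | Tripled, 0.005 |
|---|---|---|---|---|
| 0.5% | ~100% | ~100% | ~100% | ~100% |
| 1% | >99% | >99% | 91% | 76% |
| 1.5% | 97% | 90% | 27% | 11% |
| 2% | 77% | 55% | 2.5% | 0.5% |
| 3% | 20% | 7% | 0% | 0% |

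At 1%, 4 points corresponds to a relative risk of 5; at 2%, to 3. The normal approximation is rough here, with only about 11 events per arm at 1%.

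**The case against.** **The 4-point verdict within bands is not written.** The subgroup text names no margin and no pass rule, and the claim rule in Final analyses is tied to a critical value for the whole trial. Confidence intervals alone may be meant. This stands as a caution. However, what is repeated is the non-inferiority analysis, no other margin exists, and Holm-Bonferroni needs hypotheses to reject. If only intervals are intended, the Holm sentence has nothing to act on for the primary outcome and needs correcting anyway.

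**Near-certain failure in early births.** A reader might infer this, but the figures do not support it. Pooled births before 32 weeks still pass 26% of the time unadjusted, and that pool is not a planned subgroup. For the planned bands the answer depends on assumed splits. Failure is likely; it approaches certainty only for both bands passing, or under the strictest Holm step across most assumed splits.

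**An automatic pass in late births.** This too goes beyond the documents. They give no rate after 32 weeks; near 0 is only what the rounded sample-size product implies. The leniency is clear at about 1% or less and fades by 2-3%.

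**Bias from grouping on birth age.** None is shown. It would require the second injection to affect when birth occurs, or who falls into each band, and the article does not say that it does. There is also good reason to show results by birth age, since prevalence differs so much between bands.

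**No interaction test is listed.** A condensed article may leave this to the analysis plan, so its absence is not held against the protocol.

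**Conclusion.** The point holds in limited form. The protocol chooses a post-randomisation grouping over an available baseline factor and, on its natural reading, carries one absolute margin into bands whose control rates run from near 0 to 62% or more. A truly equal half dose would then more likely than not fail in the early bands under the central assumptions, while a late-band pass would say little if the control rate there is about 1% or less. The early pooled result rests on the plan's own rate and share; the band-level and late results rest on the assumed splits and rates shown. These are subgroup analyses, so the primary conclusion and the stopping rules do not depend on them. The risk is misreading a base-rate pattern as a difference in treatment effect. This should be corrected, but it does not threaten the trial.

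**What to change.** - Make gestational age at randomisation (<28 / ≥28 weeks), the stratification factor, the main pre-specified gestational-age subgroup, alongside infant sex.
- Assess heterogeneity with a treatment-by-subgroup interaction on the relative-risk scale, and show subgroup estimates with confidence intervals.
- Keep the three birth-age bands as a table labelled descriptive and based on a post-randomisation variable, with estimates and intervals but no 4-point non-inferiority verdict.
- State which hypotheses the Holm-Bonferroni family contains once that verdict is removed.

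The data are already collected, so the change is to wording. Its costs are that the clinically familiar birth-age groups become descriptive, and that the Ethics section requires approval of modifications by the steering committee, the sponsor, the French regulator and the DSMB.

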### Trial steering committee

A trial steering committee will include the coordinating investigator (TS), the scientific director (OB), the biostatistician (MU), the methodologists (CAi and CAs), and the representatives for the sponsor and for the unit in charge for the data collection and management. They will be responsible for the organization and the coordination of the trial. They will meet on a quarterly basis to review the progress of the trial.

### Safety monitoring

The trial safety will be evaluated by an independent Data Safety Monitoring Board (DSMB) at each interim analysis or when additional analyses will be requested by the sponsor or the steering committee. The DSMB will include experts in or representatives of the fields of obstetrics, neonatology, and clinical trials methodology. At the first time they met, the DSMB will validate that the methodology is compatible with the safety of the participants. Prior to each DSMB meeting, they will be provided a complete list of all adverse events, and a statistical report including description of the population and results of the interim analysis as described above. At each meeting, the DSMB may give the advice to temporarily or definitely stop the trial if in their opinion there is an unexpected or unacceptable risk for the women or the newborn, or if the interim analysis suggests the non-inferiority or futility.

### Ethics

The statistical plan has been written before the starting of the trial and approved by the steering committee, the sponsor, the French Agence National pour la Sécurité du Médicament (ANSM) and the DSMB. All modifications will be subject to the approval of these entities.

### Dissemination policy

The steering committee will determine the plan for dissemination policy. Authorship for manuscripts submitted for publication will follow the criteria defined by the International Committee of Medical Journal Editors.

## Discussion

Administration of antenatal betamethasone to women at risk of preterm delivery leads to substantial benefits for babies born preterm. Although this treatment is widely used and recommended worldwide, concerns persist regarding its long term effects because adverse events, mainly dose-related, have been reported. Because the current recommended dose of antenatal betamethasone directly derives from sheep experiments performed in the late 60’s and has not been challenged in 45 years, large randomised trials evaluating novel dose regimens are urgently needed. If a 50% reduced antenatal betamethasone dose is shown non inferior to a full dose to prevent the neonatal complications associated with preterm birth then it should be used consistently in women at risk of preterm delivery and it would be of great importance to their children.

## Abbreviations

ACS: Antenatal corticosteroids
eCRF: Electronical case report form
FiO2: Fractional inspired oxygen
IVH: Intraventricular hemorrhage
MAP: Maximum airway pressure
NEC: Necroziting enterocolitis
PMA: Post menstrual age
RDS: Respiratory distress syndrome
